## Abstract

**Background:**

Microembolism is a frequent pathological event during extracorporeal renal replacement therapy (RRT). Some previous data indicate that microemboli are generated in patients who are undergoing RRT and that these may contribute to increased cerebrovascular and neurocognitive morbidity in patients with end-stage renal disease. The current trial aims to quantify the microembolic load and respective qualitative composition that effectively reaches the intracerebral circulation in critically ill patients treated with different RRT modalities for acute kidney injury (AKI).

**Methods/design:**

The COMET-AKI trial is a prospective, randomized controlled clinical trial with a 2-day clinical assessment period and follow-up visits at 6 and 12 months. Consecutive critically ill patients with AKI on continuous renal replacement therapy (CRRT) scheduled for a switch to intermittent renal replacement therapy (IRRT) will be randomized to either switch to IRRT within the next 24 h or continued CRRT for an additional 24 h. Cerebral microembolic load will be determined at baseline, i.e., before switch (on CRRT for both groups) and on IRRT versus CRRT, whichever group they were randomized to. The primary endpoint is defined as the difference in mean total cerebral microemboli count during the measurement period on CRRT versus IRRT following randomization. Microemboli will be assessed within the RRT circuit by a 1.5-MHz ultrasound detector attached to the venous RRT tubing and cerebral microemboli will be measured in the middle cerebral artery using a 1.6-MHz robotic transcranial Doppler system with automatic classification of Doppler signals as solid or gaseous. In addition to Doppler measurements, patients will be examined by magnetic resonance imaging and neurocognitive tests to gain better understanding into the potential morphological and clinical consequences of embolization.

**Discussion:**

The results of COMET-AKI may help to gain a better insight into RRT modality-associated differences regarding microbubble generation and the cerebral microembolic burden endured by RRT recipients. Furthermore, identification of covariates of microbubble formation and distribution may help to encourage the evolution of next-generation RRT circuits including machinery and/or filters.

**Trial registration:**

ClinicalTrials.gov, ID: NCT02621749. Registered on 3 December 2015.

**Electronic supplementary material:**

The online version of this article (10.1186/s13063-018-2561-3) contains supplementary material, which is available to authorized users.

## Background

Patients undergoing renal replacement therapy (RRT) are frequently disabled, and their quality of life may be limited by dementia and silent or apparent stroke [1, 2]. Neuroimaging studies have revealed an increased prevalence of cerebral atrophy and ischemic brain lesions in RRT recipients compared to the general population following rather short periods of RRT [3–5]. In addition to traditional cerebrovascular risk factors that predispose patients undergoing RRT to increased neurological morbidity, microembolic brain injury was postulated a relevant risk factor and generation of gaseous microemboli (= microbubbles) were observed in hemodialysis circuits [6, 7]. Microemboli were also detected in arterio-venous fistulae, the subclavian vein and the carotid artery of RRT recipients. Notably, this may occur in the absence of intracardiac right-to-left shunt. Further, it is assumed that a substantial number of microemboli can evade bubble alarms in the RRT circuit, may pass the “lung barrier,” and reach the systemic arterial and cerebral circulation [8–11].

Several hypotheses exist with respect to the nature and mechanism of microemboli generation under RRT. During periods of insufficient anticoagulation on RRT circuits, the release of solid particles consisting of fibrin deposits and blood clots was postulated. More recent reports indicate that microemboli are mostly gaseous in nature and may arise either from the RRT itself (e.g., due to poor pre-dialysis de-airing, incorrect operation, malfunction of the degassing system, leakage, etc.) or appear as a result of pressure change-induced cavitation or by temperature gradients within the circuit [3, 6]. To date, the exact origin of microemboli generation and its clinical relevance are considered unclear [6].

Microbubbles from the RRT circuit travel within the bloodstream until they are trapped in the (e.g., pulmonary) microcirculation where they are slowly dissolved [6]. However, direct effects of gas bubbles in the microcirculation include ischemia and pressure changes in blood vessels and surrounding tissues [11–14]. Pressure on the endothelial cells results in increased large-pore radius and intercellular gap formation, increased hydrostatic pressure and enhanced permeability leading to interstitial edema. These effects appear potentiated by inflammatory responses and complement activation, triggering of activated polymorphonuclear leukocytes, and mast cell-derived histamine release, which results in furthermore increased vascular permeability. Activation of endothelial cells and platelets further results in activation of coagulation cascades and clot formation in direct proximity to the bubble. This may ultimately cause a (permanent) elevation of pulmonary artery pressures via increased pulmonary vascular resistance for example.

In the intensive care unit (ICU), RRT is typically provided by a continuous (CRRT) or an intermittent (IRRT) modality. Both modalities are considered equivalent in terms of clinical outcome and mortality [15–18]. A key difference between respective modalities is application of higher blood flow rates in IRRT (i.e., typical blood flow rates of 200–300 ml/min) compared to CRRT (i.e., typical blood flow rates: 100–150 ml/min). Thus, IRRT aims at higher urea solute clearance within a shorter treatment period (typically 4 h of IRRT applied).

The aim of the COMET-AKI trial is to investigate the impact of CRRT and IRRT on microbubble/cerebral microemboli generation in a cohort of critically ill patients with dialysis-dependent acute kidney injury (AKI). Our hypothesis is that microbubble generation hemodialysis circuits and the subsequent number of cerebral microemboli is related to the blood flow rate and associated arterial and venous pressures. As IRRT is associated with higher blood flow rates and increased dynamic pressure gradients, IRRT may theoretically generate higher microbubble rates and thus a larger cerebral microembolic burden.

## Methods/design

The cerebral microembolism in the critically ill with acute kidney injury (COMET-AKI) trial is a prospective, randomized controlled clinical trial with a 2-day assessment period and follow-up visits at 6 and 12 months. The primary objective is to investigate the impact of CRRT and IRRT on microbubble-/-cerebral microemboli generation in a cohort of critically ill patients with dialysis-dependent acute kidney injury.

The Cantonal Ethics Committee (CEC) has approved the study protocol (KEK No. 199/15, version 3.0, December 2015). The trial is registered at ClinicalTrials.gov (NCT02621749). The study will be performed in accordance with the study protocol and with principles enunciated in the current version of the Declaration of Helsinki, the guidelines of Good Clinical Practice (GCP) issued by the International Council on Harmonization (ICH), the European Directive on medical devices 93/42/EEC and the ISO Norm 14,155 and ISO 14971, and applicable Swiss Law. COMET-AKI is monitored by the Department of Anesthesiology and Pain Therapy of the University of Bern. The study protocol follows the Consolidated Standards of Reporting Trials (CONSORT) guidelines. All relevant data will be stored on an in-house research platform, which is a dedicated server for research data management.

### Study population and patient allocation

Consecutive critically ill patients treated with CRRT for AKI, and scheduled to be switched (as determined by the treating ICU physician in charge) to IRRT, will be randomized by an independent computer-based procedure to either switch to IRRT the next day or to continued CRRT for one additional day. Doppler measurements will be performed during CRRT for both groups before the switch (baseline, examination day 1) and after the switch (follow-up measurement, examination day 2) in the CRRT and IRRT groups, respectively. In the IRRT group, there will be a RRT pause of 12 h between CRRT termination and IRRT start in order to allow equilibration and wash out of potential CRRT-induced microemboli. Transcranial Doppler (TCD) detection of cerebral microemboli will be performed bilaterally and continuously in both middle cerebral arteries (MCAs) for 30 min. Additionally, microbubble generation will be simultaneously recorded in the RRT circuit by extracorporeal Doppler detector in the venous tubing, placed 10 cm downstream of the air detector (Fig. 1). No interventions (e.g., bolus intravenously administered (IV) drug injections, line flushing, change of infusion rate, blood sampling or other manipulations) will be allowed during Doppler examinations. At the beginning and at the end of the study period, patients will undergo routine clinical examinations to evaluate for neurological and neurocognitive disturbances. A magnetic resonance imaging (MRI) examination will be performed after inclusion of the patient in the study and again after completion of the follow-up Doppler measurements (Fig. 2).

**Fig. 1 Fig1:**
[figure not shown]
Patient flow diagram with allocation to CRRT versus IRRT. *CRRT* continuous renal replacement therapy, *IRRT* intermittent renal replacement therapy, *RRT* renal replacement therapy, *TTE* transthoracic echocardiography examination, *TEE* transesophageal echocardiography examination, *TCD* transcranial Doppler ultrasound, *MRI* magnetic resonance imaging, *CAM-ICU* Confusion Assessment Method for the Intensive Care Unit, *RASS* Richmond Agitation and Sedation Scale, *MoCA* Montreal Cognitive Assessment, *MCA* middle cerebral artery, *SF-36* Short Form (36) Health Survey

**Fig. 2 Fig2:**
[figure not shown]
Standard Protocol Items: Recommendations for Interventional Trials (SPIRIT) Figure: schedule of enrollment, interventions and assessments for the COMET-AKI trial. *CRRT* continuous renal replacement therapy, *IRRT* intermittent renal replacement therapy, *TTE* transthoracic echocardiography examination, *TEE* transesophageal echocardiography examination, *TCD* transcranial Doppler ultrasound, *MRI* magnetic resonance imaging, *CAM-ICU* Confusion Assessment Method for the Intensive Care Unit, *RASS* Richmond Agitation and Sedation Scale, *MoCA* Montreal Cognitive Assessment, *MCA* middle cerebral artery, *SF-36* Short Form (36) Health Survey

### Consent procedure

The investigators will explain to each participant the nature of the study, its purpose, the procedures involved, the expected duration, the potential risks/benefits or any potential discomfort. Each participant will be informed that the participation in the study is voluntary and that they may withdraw from the study at any time and that withdrawal of consent will not affect their subsequent medical assistance and/or treatment. All participants for the study will be provided with a Participant Information Sheet and a Consent Form describing the study and providing sufficient information for the participant to make an informed decision about their participation in the study. The formal consent of a participant/next of kin, using the approved Consent Form, will be obtained before the participant is submitted to any study-specific procedure. The participant/next of kin must read and sign the informed consent and will be given a copy of the signed document. In case of inability to give consent, the patient’s legal representative will be asked for the patient’s participation in the study. In case of deferred consent and as soon as the patient is able to give consent, the patient will be informed in detail about the study. Patients may withdraw from the study at any stage by oral or written declaration. In case of withdrawal of informed consent (or in case of non-compliance, disease progression, safety concerns) all study relevant data will be anonymized following data base closure.

### Study periods and visits

The study includes a 2-day assessment period/clinical phase and follow-up visits at 6 and 12 months. During the clinical phase, participants will attend five study visits. The overall duration of the clinical phase will be approximately 207 min for each participant.

Procedures at each visit include (Table 1):

**Table 1 Tab1:** Study measures at each visit

	Visit 1: screening	Visit 2: baseline neurocognitive examinations	Visit 3: Doppler measurement CRRT	Visit 4: randomization	Visit 5: Doppler measurement IRRT or CRRT	Visit 6: follow-up neurocognitive examinations
Duration of visit	30 min	60–120 min	90 min	30 min		60–120 min
Recruitment	X					
Consent Form	X					
Inclusion/exclusion	X					
Medical history	X					
TTE/TEE	X					
Assess vital signs		X	X	X	X	X
External randomization				X		
Clinical examination		X				X
Doppler examination			X		X	
MRI		X				X
CAM-ICU		X				X
RASS		X				X
MoCA		X				X
SF-36^a^						X

^a^After 6 and 12 months. *CAM-ICU* Confusion Assessment Method for the Intensive Care Unit, *CRRT* continuous renal replacement therapy, *IRRT* intermittent renal replacement therapy, *MoCA* Montreal Cognitive Assessment, *SF-36* Short Form (36) Health Survey, *MRI,* magnetic resonance imaging, *RASS* Richmond Agitation and Sedation Scale, *TEE* transesophageal echocardiography, *TTE* transthoracic echocardiography

Visit 1: Recruitment and screeningPatients/next of kin are recruited on site. If the treating intensivist identifies a patient whose clinical status allows switching from CRRT to IRRT, has no exclusion criteria (especially, no pathology on TTE/TEE examination) and fulfills the inclusion criteria, they will inform the patient about the study together with a study representative and will hand out the Patient Information Sheet and Consent Form (in case of inability to consent: the legal representative/next of kin will be informed). The treating intensivist then passes on this information to the principal investigator (PI) or his designee. If the patient (or the legal representative) is interested in participating, the PI will then contact the patient during his visit on the ICU (in case of inability to consent: the legal representative will be reached) to inform in detail about the study and to obtain written informed consent.Visit 2: Baseline neurocognitive examinationsThe PI (or his designee) performs the clinical examination and the neurocognitive tests.Visit 3: Doppler measurements on CRRTThe PI (or his designee) performs the Doppler measurements during CRRT therapy.Visit 4: RandomizationAt the end of examination day 1, the PI (or his designee) send out a request for patient randomization to the external institution performing the computer-based randomization (CRRT versus IRRT groups).Visit 5: Doppler measurements on CRRTThe PI (or his designee) performs the Doppler measurements during CRRT or IRRT.Visit 6: Follow-up neurocognitive examinationsThe PI (or his designee) performs the clinical examination and the neurocognitive tests. After 6 and 12 months, the SF-36 Health Survey is performed by the PI (or his designee) by telephone.

### Eligibility criteria

Participants fulfilling all of the following inclusion criteria are eligible for the study:Age aged over 18 yearsWritten informed consent as documented by the signature of the patient or their legal representative (in case of inability to give consent).

The following exclusion criteria apply:Presence of atrial septal defect (intracardiac shunting), severe aortic/mitral valve pathology or valvular endocarditis in routine transthoracic (TTE) or transesophageal echocardiography (TEE) examination (before baseline Doppler measurement)Presence of chronic atrial fibrillation or other irregular cardiac rhythmKnown cerebrovascular pathology (carotid and/or vertebral artery stenosis > 70%, cerebrovascular insult)Contraindications for MRI (e.g., pacemaker, hemodynamic instability precluding patient transfer to MRI)Missing bilateral temporal window for transcranial Doppler ultrasound (TCD) examinationAllergy to any plastic contained in the investigative devices (i.e., head frame, TCD probe) or to ultrasound gelPatients with chronic kidney disease (serum creatinine > 3 mg/dl) and/or patients undergoing chronic hemodialysis therapyPregnant or lactating patientsPatients institutionalized for neurological, psychiatric, and/or neurocognitive reasonsInability to follow the procedures of the study, e.g., due to language problems, psychological disorders, dementia, etc. of the participantParticipation in another study with an investigational drug within the 30 days preceding and during the present studyRecent hospitalization on ICU with RRT requirementPrevious enrollment into the current study

### Sample size calculation

Based on our preliminary study, [19] we expect a true difference in the mean high-intensity transient signals (HITS) value of 700 and a standard deviation of 950 HITS between the two groups of interest. With a desired power of 0.8 and an alpha of 0.05, the number of required patients is 58 (29/group). Taking into consideration a dropout rate of 15%, we plan to include a total number of patients of 66.

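### The planned total of 66 covers about 12% dropout, not the stated 15%: at 15% about 56 evaluable patients remain against the 58 required (minor, wrong as written)

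*Protocol article*

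**What the plan says.** The section *Sample size calculation* of the Protocol article sets out one chain of figures.

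- Effect, taken from a preliminary study: "we expect a true difference in the mean high-intensity transient signals (HITS) value of 700".
- Spread: "a standard deviation of 950 HITS between the two groups of interest".
- Requirement: "With a desired power of 0.8 and an alpha of 0.05, the number of required patients is 58 (29/group").
- Allowance for losses: "Taking into consideration a dropout rate of 15%, we plan to include a total number of patients of 66".

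The section does not show how the 15% was applied, and the article nowhere says that dropouts will be replaced. *Study endpoints and statistical analyses* names ANCOVA for the primary endpoint without naming the covariate. The sample size section mentions neither ANCOVA nor a correlation between baseline and follow-up counts.

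**The concern.** The required number, the dropout rate and the planned total are printed together as one argument, so they should agree. They do not: taking 15% off 66 gives fewer than 58.

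The loss would fall on the primary endpoint. By the visit schedule, patients are randomized at Visit 4 and the Doppler measurement that supplies the primary outcome follows at Visit 5, so a patient lost in between contributes no primary outcome. The plan also has almost no slack, because 29 per group is the smallest whole number that reaches 80% on the formula used. At stake is whether the stated power goes with the stated total. The estimand and the validity of the comparison are not affected.

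**Working it through.** **Inputs**, all from *Sample size calculation*: difference Δ = 700 HITS, SD σ = 950 HITS, power 0.80, α = 0.05, 29 per group (58 in total), dropout 15%, planned total 66. Sidedness is not stated. I take the test as two-sided because that reproduces the 58; a one-sided test would give 23 per group (46).

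**1. Reproduce the 58.** Normal approximation:

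n per group = 2 (1.960 + 0.842)² (σ/Δ)² = 2 (1.960 + 0.842)² (950/700)² = 28.9, rounded up to 29, so 58 in total. This matches exactly.

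**2. Apply the dropout.** For N evaluable patients after a proportion d is lost, enrol N/(1 − d):

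58/0.85 = 68.2, so 69 patients, or 70 (35 per group) with equal arms.

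The plan has 66, which is 3 or 4 fewer. The figure looks like 58 × 1.15 = 66.7 rounded down, that is, multiplying by (1 + d) instead of dividing by (1 − d). The article does not show the step, so this is an inference.

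**3. What 66 delivers.**

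- Evaluable at 15% dropout: 66 × 0.85 = 56.1, so about 56 (28 per group). If losses are rounded down to 9, 57 remain, which is still below 58.
- Largest dropout that leaves 58: (66 − 58)/66 = 8/66 = 12.1%.

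**4. Unadjusted power for 700 HITS.** By the normal approximation, power = Φ(Δ/(σ√(2/n)) − 1.960).

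| Per group | Normal approximation (reproduces the plan) | t test |
|---|---|---|
| 29 | 80.1% | 78.7% |
| 28 | 78.7% | 77.3% |

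On either basis the dropout step costs about 1.4 to 1.5 percentage points.

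**5. Difference detectable with 80% power**, normal approximation, (1.960 + 0.842) σ √(2/n):

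- 29 per group: 699 HITS
- 28 per group: 711 HITS

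The change is about 12 HITS.

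**6. What baseline adjustment could recover.** If the ANCOVA covariate is the baseline count and its correlation with follow-up is r, the residual SD is σ√(1 − r²). At 28 per group, the normal approximation gives 80% power when the SD is 700/[(1.960 + 0.842)√(2/28)] ≈ 935. Then r = √(1 − (935/950)²) ≈ 0.18. By the t test the SD is 918 and r ≈ 0.26. The article gives no correlation. For illustration, assumed values of 0.2, 0.3 and 0.5 give 80.3%, 82.4% and 88.9% by the normal approximation.

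**The case against.** The strongest reply is that this hardly matters. The shortfall is two evaluable patients, the target is given as 0.8, and 78.7% rounds to that. The planned primary analysis is also ANCOVA, and both groups have a baseline Doppler measurement on CRRT. If that baseline is the covariate, the unadjusted calculation is conservative, and a modest correlation of about 0.18 restores 80%. As a reply on severity this stands. It does not make 66 the right total, because the section takes no credit for adjustment, gives no correlation, and still names 58 as the required number.

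One might also read the 15% as a share of the 58 instead of the enrolled total. That does not rescue the figure: the 8 extra patients are 8/58 = 13.8% of 58.

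Three stronger readings are tempting, and the article does not support them.

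- *That 29 per group is itself wrong, because a t test needs 30.* The normal approximation is a standard formula and reproduces the printed 58 exactly. Preferring the t distribution is a choice of method, not the correction of an error.
- *That power falls from 80% to 77%, and the detectable difference rises from 700 to 724 HITS.* Those are t-test results at 28 per group (77.3%, 724) set against normal-approximation targets. They mix the dropout step with a change of method and roughly double its apparent effect.
- *That the primary analysis will have less than 80% power.* This is shown only for an unadjusted comparison, which is not the planned analysis.

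**Conclusion.** The point holds as a minor error in a stated figure. With 58 evaluable patients required and 15% dropout assumed, 66 is not the matching total: it leaves about 56, and it supports 58 only up to about 12% dropout. On the plan's own formula, unadjusted power is 78.7% instead of 80.1%.

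This rests on a two-sided test at 0.05, equal arms, dropout counted as a share of those enrolled, and no replacement of dropouts (none is described). The dropout arithmetic does not depend on the choice between the normal approximation and the t test. The design is not undermined and no bias follows.

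**What to change.** Restate the last sentence of *Sample size calculation* in one of two ways, neither of which needs more patients:

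- *A total of 66 patients allows for about 12% dropout while retaining 58 evaluable patients (29 per group).*
- *With 66 patients and 15% dropout, 56 remain evaluable (28 per group), giving about 79% unadjusted power (normal approximation) for a difference of 700 HITS with an SD of 950.*

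If the sponsor relies on baseline-adjusted ANCOVA to keep 80% at 15% dropout, add that the covariate is the baseline count and state the assumed baseline to follow-up correlation: at least about 0.18 by the normal approximation, or about 0.26 by the t test. That value is an assumption and needs its own justification.

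If 80% unadjusted power at 15% dropout is to be kept as written, the matching total is 69, or 70 with equal arms. The restatement costs one sentence and a slightly less favourable dropout or power figure. Only this last option costs recruitment, at 3 or 4 more patients.
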